## Abstract

**Background:**

Healthcare team communication is essential to high-quality childhood cancer care, especially during high-acuity events such as clinical deterioration and in resource-variable settings, where supportive interventions to resolve deterioration are less available. Communication quality has traditionally been understudied in these settings, and there is a notable lack of communication interventions that are appropriate and feasible in settings across resource levels. We propose addressing this challenge in this study protocol, which will co-develop and pilot a multi-level intervention to improve communication and outcomes for children receiving cancer treatment.

**Methods/design:**

This study leverages systems and implementation science methodologies to evaluate and improve communication quality in the care of hospitalized children with cancer. We will use a newly developed reliable and multilingual measure of communication quality during clinical deterioration (CritCom). In this study, we will: 1) evaluate the relationship between healthcare team communication structures (using social network analysis) and quality (using CritCom) in the care of children with cancer, with a specific focus on the impact of hierarchy and modifiable communication determinants. We will then: 2) co-develop a multilevel intervention to address challenges in communication quality across variably resourced settings, using semi-structured interviews among clinicians working in these settings and intervention mapping with a global expert panel. Finally, we will 3) test the feasibility, acceptability, appropriateness, and preliminary efficacy of this novel intervention using a cluster-randomized wait list control pilot trial in eight resource-variable hospitals providing childhood cancer care with poor team communication quality.

**Discussion:**

This project identifies modifiable determinants of communication before co-developing and testing interventions with clinicians. When completed, this study will produce an evidence-informed, multilevel intervention to improve healthcare team communication during clinical deterioration, advancing the science of team communication during cancer care, and ultimately improving survival for children with cancer.

**Trial registration:**

ClinicalTrials.gov Record NCT07083674.

Contributions to the literature
This work will provide a foundational understanding of modifiable determinants of communication that impact healthcare delivery in resource-variable settings.We will develop and test an intervention to improve healthcare team communication, a field that currently lacks effective interventions.We will use social network analysis, a systems science method, to describe structural variation in communication and compare it to organizational communication quality.This study will address two notable barriers to team communication during patient deterioration: (1) lack of understanding of specific modifiable determinants of communication structure and quality and (2) lack of appropriate, feasible, and measurable communication interventions.

## Background

To reduce global disparities in childhood cancer survival, the World Health Organization (WHO) Global Initiative for Childhood Cancer [1] and others [2] emphasize the need to improve childhood cancer treatment globally. Many hospitals providing childhood cancer care, however, face a range of resource limitations, including limited staff, supplies, and medications, challenging their ability to provide high-quality childhood cancer care and achieve this imperative [3]. A major barrier to childhood cancer survival, particularly in low-resource settings, is treatment-related mortality, or death during cancer treatment [4]. Clinical deterioration, defined as a decline in a patient’s clinical state that requires rapid identification and intervention, is a common cause of morbidity and mortality in children with cancer [5, 6]. Our prior work demonstrated a 30% mortality among pediatric oncology patients with deterioration in low-resource hospitals [7–13]. To date, however, there are limited effective interventions to improve outcomes for children with cancer who experience deterioration in resource-variable hospitals [14].

Optimal outcomes during clinical deterioration in children with cancer require excellent care coordination across multiple teams, necessitating high-quality team communication [15]. Over 70% of treatment delays, preventable harm, and death occur due to poor communication [16–23]. Prior studies have demonstrated that better communication leads to safer care, fewer medication errors [24], higher rates of rescue [25], and increased consistency in patient care across clinical teams [26]. High-quality communication between clinicians (e.g., physicians, nurses, pharmacists, respiratory therapy, etc.) directly impacts how teams utilize available resources and skills to identify and manage deterioration, thereby preventing mortality and improving health outcomes [27, 28]. Deterioration events, however, are highly stressful for clinical team members due to high patient acuity and time pressures, resulting in a risk of ineffective communication and lack of psychological safety, conceptualized as having a sense of safety in speaking up [16, 22]. Low-resource settings face additional communication challenges, including hierarchical systems, lower staff-to-patient ratios, and varying roles and responsibilities [29]. Addressing healthcare team communication, especially during acute events like clinical deterioration, offers a theoretically effective, low-cost intervention to improve childhood cancer outcomes across different settings. Previously studied interventions to improve pediatric oncology communication, however, focus on planned, controlled settings such as rounds or tumor boards and have been primarily developed and tested in high-resource settings [19, 30–33]. There is an urgent need for effective communication interventions to target complex systems and subsequently improve outcomes related to deterioration.

To improve communication in the care of children with cancer, we must identify modifiable factors that affect the quality of team communication [16, 21, 34, 35]. **“**Team communication” in this context must focus on the process of information exchange among the entire healthcare team, encompassing the quality of this exchange both between clinicians of different *professions* (physicians, nurses, respiratory therapist, social workers, etc.) and different *disciplines*(oncology, intensive care, surgery, etc.). However, there is a lack of a robust understanding of modifiable components of healthcare team communication structure and quality that can be targeted with interventions. Few effective interventions improve team communication and those that exist were primarily developed in high-resource settings [19, 30–33]. Low-resource settings are understudied [36], creating disparity between the high burden of childhood cancer mortality and poor understanding of communication determinants in these settings. This highlights a need for co-developed communication interventions appropriate for resource-diverse settings [37–39].

To address this knowledge gap, the TeamTalk study will develop and test a multilevel intervention that focuses on modifiable determinants of healthcare team communication structure and quality in global pediatric oncology hospitals, aiming to improve childhood cancer outcomes*.* To achieve this goal, we will 1) evaluate the relationship between team communication structure and quality in the care of children with cancer, 2) co-develop a multilevel intervention to improve communication quality in resource-variable hospitals, and 3) test the feasibility, acceptability, appropriateness, and preliminary efficacy of this intervention in resource-variable hospitals through a pilot cluster-randomized wait list control trial.

## Methods and design

TeamTalk is an observational, formative study of team communication in resource-variable pediatric oncology hospitals, followed by intervention co-development and pilot testing (Table 1). We will engage members of the global oncology community to assess the relationship between team communication structure and quality (Aim 1) and use a mixed-method approach to co-develop and test an intervention to address these challenges across settings (Aims 2/3).

**Table 1 Tab1:** Overview of study aims

Overall Question: What are common modifiable determinants of healthcare team communication during deterioration and how might interventions target these determinants to improve outcomes for children with cancer in resource-variable settings?		
Aim 1: Communication structure and quality	Questions	What is the relationship between structure and quality of team communication around deterioration in children with cancer?
	Method	Cross sectional social network analysis from 10 high- and 10 low-quality communication hospitals selected from previous cross-sectional data (total *n* = 20)
	Outcome	Empirical relationship between communication quality, communication structures, and provider and hospital level determinants
Aim 2: Develop intervention to improve communication	Question	What are potential multi-level interventions to address common modifiable challenges to communication quality across both high- and low- resource hospitals?
	Method	(1) Sequential mixed methods study using quantitative data from Aim 1 supplemented by qualitative interviews with clinicians and (2) implementation mapping with global experts to co-develop an intervention to address common communication challenges
	Outcome	Multi-level intervention co-developed and selected for pilot testing
Aim 3: Pilot trial of communication intervention	Question	Is the identified intervention effective to improve communication quality and provider and patient outcomes while being perceived as feasible and acceptable by providers?
	Method	Pilot identified multilevel intervention at 8 resource-variable hospitals using a wait list controlled, cluster randomized trial
	Outcome	Identify feasibility, acceptability, appropriateness, and preliminary efficacy, of intervention to improve communication quality during deterioration

### Conceptual framework

This study is informed by implementation science, health services research, and network communications theories, specifically the cancer Multiteam System (cMTS) framework (Fig. 1) [40, 41]. This conceptual framework illustrates how complex teams collaborate to deliver coordinated cancer care, highlighting the importance of effective communication structures and quality in care delivery. cMTS informs this study through its description of care processes and how teams are composed and organized, including team structure and hierarchy. Within the cMTS framework, communication is described as part of the processes of teamwork, while structure is an input. Care processes include both teamwork between and across teams as well as tasks that are accomplished through care delivery. These result in multilevel outcomes, including clinical patient outcomes, provider outcomes (burnout and job satisfaction), and unit/team outcomes (guideline adherence and efficiency of care) [40, 41].

**Fig. 1 Fig1:**
[figure not shown]
Overview of conceptual framework for this research, focusing on assessing communication structure and quality within resource-variable settings. This is adapted from the cancer Multiteam System (cMTS) framework

Communication can be conceptually divided into two components: (1) quality of communication and (2) structure of communication [42, 43]. High-*quality* communication improves patient care, and we conceptualize this in alignment with the CritCom framework, a novel, reliable, multilingual measure of team communication quality comprised six domains (Fig. 2) [44, 45]. Less is known about how communication *structures*can promote enhanced care, although examples of this include hierarchies, standard communication norms, and escalation protocols. For this study, we conceptualize communication structure as informed by network theory. Network communication theory describes the structures of communication to understand individual interactions, feedback, and behavior constraints among those involved within complex systems [46–48]. While network theory views each individual actor as following fairly simple rules or behaviors, complexity occurs when these simple behaviors multiply into a system of behaviors [49, 50]. Network communication theories point to network analysis as the appropriate methodology to understand communication structure in complex healthcare systems.

**Fig. 2 Fig2:**
[figure not shown]
CritCom measure domains of quality team communication

Using these complementary frameworks, we posit that communication structure and quality interact to directly impact the quality of patient care. For example, lack of clarity and poor tone (communication quality) can impact clinician understanding of patient status and delay necessary intervention (care quality). Similarly, communication that must flow through a single lead physician has a high degree of hierarchy (communication structure), which can delay the flow of communication and necessary intervention, thus impacting patient outcomes. These interactions also impact providers, as poor communication experiences contribute to increased burnout and intentions to leave. This, in turn, further impacts patient outcomes, including safety events, mortality, and morbidity.

Our study aims (Table 1) are directly incorporated into this conceptual framework. Aim 1 focuses on the interrelationship between communication structure and quality to identify determinants of high-quality team communication. Aim 2 focuses on co-developing an appropriate multilevel intervention to target modifiable determinants of communication. Aim 3 tests the intervention’s feasibility and preliminary efficacy to improve team communication, and provider and patient outcomes in a pilot trial.

## Setting

The proposed work will be conducted in collaboration with resource-variable pediatric oncology hospitals participating in the St. Jude Global Alliance [2], an international global health research and advocacy program that aims to strengthen care for children with cancer and other catastrophic diseases through innovative interventions, education, research, and team collaboration. Currently, the alliance has collaborators from more than 300 institutions in 77 countries. Over 110 St. Jude Global Alliance hospitals have completed the CritCom survey, and many others have participated in other large studies evaluating pediatric oncology care in resource-variable settings [51–56]. Hospitals with prior CritCom participation will be eligible sites for this study. While most hospitals are located in low- and middle-income countries, several are situated in World Bank-designated high-income countries. Aligned with our previous work, we will include hospitals self-identifying as having limitations in a broad range of resources, including inadequate nursing and physician staffing to identify and manage clinical deterioration events, limited Pediatric Intensive Care Unit space to accommodate children with cancer, and patients with low socioeconomic, educational, and nutritional indicators [3, 57–59]. These challenges result in an increased frequency of deterioration events with high mortality [12, 13], and their involvement enriches our study of communication across a range of resource limitations.

### Study measures

Study measures (Table 2) align with our conceptual model, including measures of care inputs, team communication, care processes, and multilevel outcomes.

**Table 2 Tab2:** Overview of study measures

Data Domain	Measures	Data Collection Methods
Communication quality	CritCom (6 domains, 30 questions)^a^	- Individual survey, distributed confidentially and electronically through REDCap [60] - Distributed to all frontline clinical staff caring for children with cancer at risk of deterioration at each participating hospital - 3 weeks for data collection with weekly reminders
Individual demographics	6 questions on role, unit worked, length of experience, sex, and hospital of employment	
Provider outcomes	Questions about burnout, intent to leave, and job satisfaction	
Hospital characteristics	Hospital type, funding, bed capacity, pediatric oncology/critical care staffing, annual new diagnoses, and region	- Collected and confirmed by local site lead
Communication structures	Social network survey using a roster-based approach asking clinicians about overall communication patterns and changes during deterioration events^a^	- Individual survey distributed confidentially through REDCap, 20–30 min. to complete - Distributed to all frontline clinical staff caring for children with cancer - 3 weeks for data collection with weekly reminders
Challenges to communication and potential communication interventions	Perspectives of clinicians on communication challenges related to hospital and individual barriers, as well as potential interventions to improve team communication during care delivery	- Semi structured interviews of frontline clinicians caring for children with cancer (physician, nurse, respiratory therapy, etc.) - Purposive sample for diversity including country income level, hospital size, professional role, etc
Intervention feasibility, acceptability, and appropriateness	After intervention implementation, measures to assess how individual clinicians view the feasibility of intervention and their ratings of how appropriate and acceptable it is for them to receive the intervention in their setting	- Individual survey, distributed confidentially through REDCap, 5 min. to complete - Distributed to all frontline clinical staff caring for children with cancer at 8 hospitals - 3 weeks per hospital for data collection, with weekly reminders
Patient Outcomes	Clinical Deterioration Events (CDEs) [13] defined as an unplanned transfer to a higher level of care (i.e., ICU), use of an ICU intervention on the ward (vasoactive infusion, invasive or noninvasive mechanical ventilation, or cardiopulmonary resuscitation), or a ward death in a patient without limitations on resuscitation	- Prospective de-identified registry of all CDEs in hospitalized pediatric oncology patients collected by the site team - For each CDE, a de-identified case report form is completed by local site leads and entered in REDCap database by a study team member - Data analysis checks for missing and incorrect values assure data quality - Pre and post intervention measurements

^a^CritCom and the network survey will be collected concurrently during Aim 1, with CritCom collected alone during Aim 3

#### Social network survey

A social network survey will be conducted among 20 hospitals. These hospitals have previously completed CritCom and all provide pediatric cancer care. All critical care and ward clinicians caring for children with will be surveyed. Questions relate to communication patterns with all other clinicians sharing the same shift, communication during deterioration, role-based communication patterns, and other questions about the structure of team communication in their setting.

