#### Participant recruitment

Within each participating hospital, all clinicians who care for children with cancer at risk of deterioration will be eligible. A roster of all clinicians will be developed by site leads and revised with input by the study team, as is standard in network data collection. Individuals will be consented into this aim, and their participation will conclude at the end of the social network analysis and CritCom survey. Participation will be voluntary. We will provide incentives appropriate for each region for individuals who complete the assessment.

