#### Data collection

Participants will be asked to complete a single survey containing the social network and CritCom questions. The social network survey inquires about communication patterns between individuals in routine care and how these patterns change when a patient is experiencing clinical deterioration. Participants will respond to questions including their communication contacts, and frequency of communication for both routine inpatient care and deterioration events. The CritCom assessment portion measures communication quality using 5-point Likert scores across 6 domains [44, 45]. The survey will be administered through email online methods including email and WhatsApp, and participants will complete the survey online using REDCap. CritCom surveys are completed individually and averaged to obtain an institutional overall CritCom score and scores for each of six domains.

*Data management and analysis*. Data will be cleaned, managed, and analyzed in R [62]. The analysis will consist of two phases. First, we will produce network maps of team communications within each hospital. These maps will highlight how each team member communicates with other professions and disciplines at each hospital. Second, we will produce descriptive network statistics for each hospital, focusing on the interconnectedness, cross-profession connection patterns, and betweenness centralization [63–66]. Producing these statistics will identify any subgroups or other unique network patterns that arise within each of the hospital systems [64]. We are particularly interested in the network measure of betweenness centralization, which characterizes the hierarchical nature of clinical communication networks. Finally, we will build statistical models (exponential random graph model) [67] and explore the association of quality (CritCom scores) with structure (i.e., density) using the hospital-specific communication networks. This statistical model will help assess the probability that nodes (individuals) will have ties between them, allowing for the evaluation of predictors of communication based on individual characteristics and dyad attributes.

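### Aim 1 describes the network tie both as same-shift and as whole-roster; if ties are shift-limited, density, and under largely fixed shifts centralization, partly reflect the rota

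*Protocol article*

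**What the plan says.** The protocol article describes the same survey with two scopes.

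- **Study measures, Social network survey:** "Questions relate to communication patterns with all other clinicians sharing the same shift". The sentence goes on to list "communication during deterioration, role-based communication patterns, and other questions about the structure of team communication in their setting", with no shift limit on those items.
- **Study measures, Table 2:** "Social network survey using a roster-based approach asking clinicians about overall communication patterns and changes during deterioration events".
- **Aim 1, Participant recruitment:** "A roster of all clinicians will be developed by site leads and revised with input by the study team". This sets the node set as every eligible clinician in the hospital.
- **Aim 1, Data collection:** "Participants will respond to questions including their communication contacts, and frequency of communication for both routine inpatient care and deterioration events", again with no shift limit.

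The analysis paragraph under Aim 1, Data collection works at hospital level: "we will produce descriptive network statistics for each hospital". It singles out "the network measure of betweenness centralization, which characterizes the hierarchical nature of clinical communication networks" and names density as an example of the structure to be related to CritCom. The exponential random graph model may use individual and dyad attributes, but shared shift is not named as one. The individual items in Table 2 cover role, unit, experience, sex and hospital, but not shift.

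**The concern.** A network statistic is interpretable only if the relation asked about and the set of people over whom it is counted have the same scope. Here one description limits the relation to shift-mates, while the node set is the whole roster. If ties follow the narrower description, two clinicians who never share a shift cannot report a tie. That pair is then a structural zero, yet in a hospital-wide density it looks the same as two co-workers who do not talk. A person who works across shifts can also become the only path between teams, and so acquire high betweenness without any hierarchy within a shift.

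The number of shift teams, the degree of rotation and the number of bridging staff plausibly differ between the 20 hospitals, because the Setting section selects for staffing limitations. Part of an association between structure and CritCom could then be a staffing-pattern effect. Aim 1 results enter the Aim 2 joint displays and help define the problem for intervention mapping, so a misread structure measure could influence which determinants are regarded as modifiable.

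**Working it through.** The article gives no network figure for Aim 1, so there is no stated value to reproduce. The question is how far a shift-limited tie would move the two named statistics when communication behaviour is held constant.

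**Inputs, all assumed** (the article gives no roster size, shift pattern or tie rate): an undirected network of *n* = 60 clinicians; *k* = 1 to 4 shift teams, assigned at random; a share *r* of cross-shift pairs who also work together at times (0, 0.5 or 1); 0 or 2 staff who overlap all shifts; tie probability *p* = 0.6 for every pair able to share a shift, which means no hierarchy. A comparison network has true hierarchy: two hubs with tie probability 0.9 and all other pairs 0.1. Simulated values are means of 30 replicates.

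**Density.** Without bridging staff, a pair can share a shift with probability 1/*k* + (1 − 1/*k*)*r*, so

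expected density = *p* × [1/*k* + (1 − 1/*k*)*r*].

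| Shift teams | r = 0 | r = 0.5 | r = 1 |
|---|---|---|---|
| 1 | 0.60 | 0.60 | 0.60 |
| 2 | 0.6 × 0.500 = 0.30 | 0.6 × 0.750 = 0.45 | 0.60 |
| 3 | 0.6 × 0.333 = 0.20 | 0.6 × 0.667 = 0.40 | 0.60 |
| 4 | 0.6 × 0.250 = 0.15 | 0.6 × 0.625 = 0.375 | 0.60 |

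The simulated values agree (for example 0.448, 0.399 and 0.374 at *r* = 0.5). Density falls with the number of teams unless rotation is full.

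**Betweenness centralization.** Freeman's index is Σ(C_max − C_i)/(*n* − 1), where C_i is the betweenness of clinician *i* divided by (*n* − 1)(*n* − 2)/2. Simulated means with no hierarchy:

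| Shift teams | r = 0, no bridging staff | r = 0, two bridging staff | r = 0.5, two bridging staff | r = 1, two bridging staff |
|---|---|---|---|---|
| 1 | 0.004 | 0.004 | 0.004 | 0.004 |
| 2 | 0.003 | 0.273 | 0.010 | 0.004 |
| 3 | 0.003 | 0.364 | 0.018 | 0.004 |
| 4 | 0.004 | 0.399 | 0.022 | 0.004 |

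For scale, true two-hub hierarchy on a single shift gives about 0.36. Fixed shifts with two bridging staff can therefore produce, with no hierarchy at all, a value as large as real hierarchy. With two to four teams and at least half of cross-shift pairs overlapping, true hierarchy gives 0.37 to 0.44, clearly separate from the 0.02 or less seen without hierarchy.

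**Between these cases.** A second set of assumptions (*p* = 0.5, three bridging staff, two to four teams, no hierarchy) gives centralization of 0.20 to 0.29 with fixed shifts, 0.11 to 0.20 when 5% of cross-shift pairs overlap, 0.03 to 0.07 at 25%, and about 0.02 at 50%. The centralization artefact fades quickly with rotation. Density does not recover as fast: at 50% overlap it is still 0.33 to 0.39, against 0.50 with one common shift.

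**The case against.** The strongest reply is that the same-shift phrase is one item in a list. The rest of that sentence, Table 2 and the Aim 1 data collection text carry no shift limit, and no section says the same-shift item generates the ties. Sharing a shift could also mean ever working alongside someone. This reply stands against two stronger readings that a reader might infer. One is that the survey asks only about shift-mates, which the article's other descriptions contradict. The other is that density and centralization measure the rota instead of hierarchy. For centralization that needs largely fixed shifts and a few bridging staff, and the article documents neither.

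A second reply is that exact item wording belongs to the survey instrument or full protocol, that the model already allows dyad attributes, and that Aim 2 has its own safeguards: interviews that ask about hierarchy, expert-panel review and a modified Delphi. This limits the likely harm. It does not remove the point, because the two scopes are both stated in the article. Staffing and bed capacity are collected at hospital level, but they do not show which pairs could have shared a shift. On the listed data, that could not be recovered after collection.

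**Conclusion.** The concern holds as an inconsistency in the scope of the tie, with a conditional consequence. If ties are shift-limited, density depends on the number of shift teams unless rotation is full: 0.15 to 0.30 with two to four fixed shifts, and about 0.37 to 0.45 at half overlap, against 0.60 with one shift. Centralization is inflated (0.27 to 0.40) only when shifts are largely fixed and a few staff bridge them. It stays near zero without bridging staff and is little affected under substantial rotation. These figures rest on the assumed roster size, tie probability and shift patterns. The article gives none of these, so the actual size is unknown and could be nil if the whole-roster definition is the one used. The consequence is confined to the exploratory association between structure and quality in Aim 1 and its use in Aim 2. The Aim 3 randomised comparison and its outcomes are not affected.

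**What to change.** 1. Reconcile the Social network survey paragraph with Table 2 and the Aim 1 sections by stating one tie definition, for example communication with any roster member over a fixed recent period.
2. Under either definition, have the site lead add each clinician's usual shift or team to the roster, and include shared shift as a dyad attribute in the exponential random graph model.
3. If ties remain shift-limited, compute density over pairs able to share a shift, and report centralization within shift teams as a check before reading the hospital-level value as hierarchy.

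The cost is a wording change and one extra roster column, both before Aim 1 data collection. Recall over a longer period is slightly less exact than for a single shift, and a usual shift is only approximate for staff who rotate.
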